### **Exclusion Criteria**

- Any clinically significant abnormal finding on screening biochemistry or haematology blood tests or on urinalysis
- Previous history of TB disease and/or treatment
- Any AIDS defining illness
- CXR showing TB or evidence of other active infection
- Prior receipt of a recombinant MVA or Fowlpox vaccine
- Use of any investigational or non-registered drug, live vaccine or medical device other than the study vaccine within 30 days preceding dosing of study vaccine, or planned use during the study period
- Administration of chronic (defined as more than 14 days) immunosuppressive drugs or other immune modifying drugs within six months of vaccination. (For corticosteroids, this will mean prednisolone, or equivalent,  $\geq 0.5$  mg/kg/day. Inhaled and topical steroids are allowed.)
- History of allergic disease or reactions likely to be exacerbated by any component of the vaccine, e.g. egg products
- Presence of any underlying disease that compromises the diagnosis and evaluation of response to the vaccine (including evidence of cardiovascular disease, history of cancer (except basal cell carcinoma of the skin and cervical carcinoma in situ), history of insulin requiring diabetes mellitus, any ongoing chronic illness requiring ongoing specialist supervision (e.g., gastrointestinal), and chronic or active neurological disease)

- History of  $\geq 2$  hospitalisations for invasive bacterial infections (pneumonia, meningitis)
- Suspected or known current drug and/or alcohol abuse
- Seropositive for hepatitis B surface antigen (HBsAg) and/ or hepatitis C (antibodies to HCV)
- Evidence of serious psychiatric condition
- Any other on-going chronic illness requiring hospital specialist supervision
- Any confirmed or suspected immunosuppressive or immunodeficient condition, **other than** HIV infection, such as asplenia
- Evidence of hepatomegaly
- Administration of immunoglobulins and/or any blood products within the three months preceding the planned administration of the vaccine candidate
- Pregnant/lactating female and any female who is willing or intends to become pregnant during the study
- Any history of anaphylaxis in reaction to vaccination
- PI assessment of lack of willingness to participate and comply with all requirements of the protocol, or identification of any factor felt to significantly increase the participant's risk of suffering an adverse outcome

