**Group 2 (HIV infected on ARV):**

- CD4 count less than 300 or CD4 count nadir less than 100
- Detectable HIV viral load at  $>75$  copies/ml

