## 5 STUDY ENROLLMENT AND SCHEDULE OF FOLLOW-UP VISITS

Subjects who match all inclusion and exclusion criteria and who are available for the follow up will be invited to take part after screening. Subjects will attend the Bacteriology and Virology Laboratory at Le Dantec Teaching Hospital for vaccination. All volunteers will be vaccinated with MVA85A and will not be randomised.

The following table illustrates the sequence of events from screening, through vaccination (day 0) and subsequent follow-up visits (explained in more detail in the text that follows):

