**Table 3: Temporal course of blood investigations:**

| Test/Timepoint  | Volume (ml)                | Scr   | 0     | 7     | 28    | 84    | 168 (+/- 14) | 12.1 ^ (168-350) | 7 ◇ | 28    | 84    | 168   | Total (ml) |
|-----------------|----------------------------|-------|-------|-------|-------|-------|--------------|-----------------------------|----------------|-------|-------|-------|------------|
| FBC             | 4                          | X     |       | X     |       | X     |              | X                           | X              |       | X     |       | 20-24      |
| BioChem         | 4                          | X     |       | X     |       | X     |              | X                           | X              |       | X     |       | 20-24      |
| HBV/HCV/β-HCG   | 4                          | X     |       |       |       |       |              |                             |                |       |       |       | 4          |
| HIV             | 4                          | X     |       |       |       |       |              |                             |                |       |       |       | 4          |
| CD4             | 4                          | X     | X     | X     | X     | X     | X            | X                           | X              | X     | X     | X     | 40-44      |
| Viral Load      | 8                          | X     | X     | X     | X     | X     | X            | X                           | X              | X     | X     | X     | 80-88      |
| HLA             | 4                          |       |       |       | X     |       |              |                             |                |       |       |       | 4          |
| Research Bloods | 20-30 (16-26 at screening) | X     | X     | X     | X     | X     | X            |                             | X              | X     | X     | X     | 216-326    |
| TOTAL           | –                          | 44-54 | 32-42 | 40-50 | 36-46 | 40-50 | 32-42        | 0-20                        | 40-50          | 32-42 | 40-50 | 32-42 | 364-484    |

◇ Note that the days from this point on are shown as days after the second vaccination

^ FBC, Biochemistry, CD4 and VL will be repeated for exclusion criteria evaluation if a subject has been for their 6 month visit but was not vaccinated because the 6 month visit was prior to the second vaccination amendment.

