**Contraindications to Vaccination**

The following adverse events constitute contraindications to administration of vaccine at that point in time; if any one of these adverse events occurs at the time scheduled for vaccination, the subject may be vaccinated at a later date, or withdrawn at the discretion of the investigator. The subject must be followed until resolution of the event as with any adverse event.

- Acute disease at the time of vaccination. (Acute disease is defined as the presence of a moderate or severe illness with or without fever.) All vaccines can be administered to persons with a minor illness such as diarrhoea, mild upper respiratory infection with or without low-grade febrile illness, i.e., temperature of  $<37.5^{\circ}\text{C}$ ).
- Temperature of  $\geq 37.5^{\circ}\text{C}$  at the time of vaccination

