**Booster vaccination:**

- For Group 1, if Day 168 visit is before Protocol 2.0 amendment, the second vaccination will be given between days 168-350 (visit 12.1). However, before the subject receives the second vaccination, all inclusion and exclusion criteria except number 5 (Prior receipt of a recombinant MVA or Fowlpox vaccine) will be reviewed to check if the subject is still eligible to receive the vaccine. At this additional visit, 20 ml of blood will be collected to perform FBC, Biochemistry, CD4 and VL tests. Urinalysis, to exclude glycosuria and significant proteinuria will be performed. If any exclusion criterion are met except number 5, the subject will not be revaccinated.
- For Group 2, the second vaccination will be given at Day 168 (+/- 14 days)
- A photograph of the vaccination site will be taken after revaccination. The subject will only be identifiable by a unique study number.

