**Procedures to be Followed in the Event of Abnormal Laboratory Test Values or Abnormal Clinical Findings**

Any subject with a clinically significant finding (e.g. hypertension) or abnormal biochemical or haematological may have the test repeated to ensure this was not a single occurrence prior to inclusion. If the test remains clinically significant the subject will be excluded from the study and referred to their HIV physician or GP as appropriate for further investigation and management with the permission of the volunteer. If occurring during the trial, tests may be repeated to verify the results, and further tests may be instigated to establish causality. The volunteer will be kept informed of all such occurrences and advised of actions to be taken, and their verbal/written consent taken for extra tests where appropriate.

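### The eligibility review and no-revaccination rule before dose 2 are written only for Group 1 at visit 12.1, so up to 12 Group 2 second doses have neither

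*Protocol*

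**What the plan says.** The Booster vaccination text in Section 5 has separate bullets for the two groups.

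- **Group 1.** The bullet applies to subjects whose Day 168 visit came before the Protocol 2.0 amendment. They are boosted at an additional visit, 12.1, between Days 168 and 350. Every entry criterion is rechecked first, apart from exclusion 5 (earlier receipt of an MVA or fowlpox vaccine). Blood and urine tests follow, and then the rule: "If any exclusion criterion are met except number 5, the subject will not be revaccinated".
- **Group 2.** The bullet reads "For Group 2, the second vaccination will be given at Day 168 (+/- 14 days". It sets no condition beyond the window.

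The footnote to Table 3 ties the repeat bloods to the same visit 12.1 situation: "FBC, Biochemistry, CD4 and VL will be repeated for exclusion criteria evaluation". Table 2 likewise restricts visit 12.1 to subjects whose six-month visit preceded the amendment.

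Elsewhere the criteria operate at entry. Section 5 opens with "Subjects who match all inclusion and exclusion criteria and who are available for the follow up will be invited to take part after screening". The Group 2 exclusions include "CD4 count less than 300 or CD4 count nadir less than 100" and a viral load above 75 copies/ml. The general exclusions include "Previous history of TB disease and/or treatment".

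**The concern.** The primary objective is the safety of two injections. For visit 12.1 the sponsor has already decided that a subject who now meets an exclusion should not receive the second one. Nothing in the Protocol explains why that should not hold in Group 2, whose members can also change status in the six months between doses. Followed as written, a Group 2 subject whose CD4 count has fallen below 300 by Day 168 is boosted, and the investigator has no rule to rely on for withholding the dose. Any Group 1 subject boosted at visit 12 itself is in the same position. The Protocol does not say whether there are any.

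**Working it through.** **1. Which second doses are covered.** The Protocol Summary plans 12 subjects on ARVs and 12 not on ARVs. The Rationale says Group 2 consents to two doses, whereas Group 1 subjects already recruited are asked and are under no obligation.

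| Second dose | Criteria review | Rule to withhold |
|---|---|---|
| Group 1 at visit 12.1 | Yes | Yes |
| Group 1 at visit 12 (number not stated, possibly 0) | No | No |
| Group 2 at visit 12 (up to 12) | No | No |

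The total of 24 second doses is a maximum, because Group 1 boosts are optional and subjects in either group may withdraw.

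**2. Whether another section fills the gap.**

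- Contraindications to Vaccination: "Acute disease at the time of vaccination", defined as moderate or severe illness, and a temperature of 37.5 °C or more. The investigator may defer or withdraw the subject. This covers part of the gap.
- Table 2 and Reporting of Pregnancy (Section 8): a urine pregnancy test on the vaccination day. This also covers part.
- Abnormal laboratory values and clinical findings (Section 8): a confirmed abnormality before inclusion excludes the subject. Afterwards, "If occurring during the trial, tests may be repeated to verify the results", with no consequence for dosing.
- Local Safety Monitor and Halting Rules: these act on the whole study after an SAE or a SUSAR, not on an individual dose.
- Day 168 visit text: CD4 and viral load are drawn, but nothing says the results must be seen before the injection or which result would stop it.

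**3. Tests available at each boosting visit (volumes from Table 3).**

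- Day 168: CD4 4 + viral load 8 + research 20 to 30 = 32 to 42 ml, the printed total. No FBC or biochemistry is drawn.
- Visit 12.1: FBC 4 + biochemistry 4 + CD4 4 + viral load 8 = 20 ml, again as printed.

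The last scheduled FBC and biochemistry before a Day 168 boost are therefore those of Day 84.

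**4. Age of the Day 84 results at the boost.** The windows are 84 ± 7 and 168 ± 14 days.

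- Nominal: 168 − 84 = 84 days.
- Minimum: (168 − 14) − (84 + 7) = 154 − 91 = 63 days.
- Maximum: (168 + 14) − (84 − 7) = 182 − 77 = 105 days.

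For dose 1, the screening visit may be up to 90 days before vaccination. Boost days that respect the same 90-day limit run from 154 to the smaller of 182 and the Day 84 visit day + 90:

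- visit on day 77: 154 to 167 (14 days)
- visit on day 84: 154 to 174 (21 days)
- visit on day 91: 154 to 181 (28 days)

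**5. Repeat draws if boosts are not scheduled with this in mind.** Assume both visit days are spread evenly over their windows. With v the shift of the Day 84 visit (−7 to +7), the boost days giving results older than 90 days number 8 − v. The sum over v is 15 × 8 = 120, out of 15 × 29 = 435 day pairs. 120/435 = 0.276, and 0.276 × 12 = 3.3 subjects. The possible range is 0 (all on nominal days) to 12, so the figure is only indicative.

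**The case against.** The best case for the plan is that Group 2 is boosted inside close scheduled follow-up, with CD4 and viral load at Days 7, 28 and 84 and FBC and biochemistry at Days 7 and 84, whereas visit 12.1 may come as late as Day 350. That explains why extra bloods are scheduled at 12.1, and the Day 168 laboratory schedule is not the fault here. It does not explain leaving out the rule. The 12.1 window opens at Day 168, inside Group 2's window of Days 154 to 182, so two subjects boosted on the same study day can be treated differently.

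Some exclusions are also timed to dosing by their own wording (immunosuppressive drugs, blood products, investigational products) and can be read as applying to each dose. That is partial cover at most. The full list cannot apply to dose 2 without setting aside exclusion 5, which every previously vaccinated subject meets, and that exception appears only in the Group 1 bullet.

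Two stronger readings are tempting, and the documents do not support them.

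- A reader might infer that a Group 2 subject who has developed TB must be boosted unless the investigator departs from the Protocol. The contraindications are written generally, and they already permit deferral or withdrawal for moderate or severe active TB or AIDS-defining illness.
- A reader might infer that boosting after loss of virological control is a clear safety hazard. Group 1 receives the same dose with viral loads up to 100,000 copies/ml, so the 75 copies/ml limit appears largely to define the suppressed group. Section 1 also reports no viral load rise with MVA vaccines in people established on ARVs.

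Last, withholding doses has a price: each one removes 1/12, about 8%, of Group 2's planned two-dose data.

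**Conclusion.** The gap is real and should be corrected, but it is moderate. Up to 12 Group 2 second doses, plus an unstated and possibly zero number of Group 1 boosts at visit 12, have no eligibility review and no eligibility-based rule for withholding the dose. This follows from the text and rests on no numerical assumption.

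The uncovered cases are mainly a CD4 count below 300; clinically significant laboratory abnormalities; TB or an AIDS-defining illness since dose 1 that is mild, treated or resolved; and new immunosuppression. Loss of viral suppression belongs on the list mainly because it takes the subject outside the group definition. How many subjects would meet an exclusion by Day 168 is not given, and no estimate is offered. A statistical analysis plan would not normally settle who may be dosed, so its absence from view does not account for the gap.

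**What to change.** Take two sentences out of the visit 12.1 bullet, the criteria review that omits exclusion 5 and the no-revaccination rule, and make them govern every second dose in both groups. Leave the visit 12.1 bloods as they are.

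At visit 12, base the review on:

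- the interim history;
- a dipstick on a urine sample from every subject, since Table 2 currently marks urinalysis there as a pregnancy test for women only, while the first exclusion includes urinalysis findings;
- the most recent CD4, viral load, FBC and biochemistry, no more than 90 days old as for dose 1. Any result that is older or out of range is repeated before dosing, within the ± 14 day window where possible.

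Subjects not revaccinated stay in follow-up, and their number and the reasons are reported by group.

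No routine extra visit is needed, because at least 14 in-window boost days always satisfy the 90-day limit. The cost is a dipstick, occasional repeat draws (4 + 4 = 8 ml for FBC and biochemistry, or 20 ml with CD4 and viral load) and possibly a few fewer second doses. A remaining limit is that results up to 90 days old can miss a change after Day 84. Reading the CD4 and viral load before the injection, from a draw a few days earlier, would close that at the price of an extra attendance.

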**Days 1–6 post second vaccination (+/- 0 day)**

- An interim history will be taken and, if considered necessary a physical examination emphasizing any acute complaints will be performed. Vital signs will be checked and documented

- The injection site will be inspected and the largest diameter of any hardness or redness present, as well as the degree of pain reported for the time of the visit will be documented into the CRF.
- Solicited adverse events (local and general) that may have occurred since the vaccination will be documented in the CRF.

**Day 7 (+/- 1 day) post second vaccination**

- An interim history will be taken and, if considered necessary a physical examination emphasizing any acute complaints will be performed. Vital signs will be checked and documented
- The injection site will be inspected and the largest diameter of any hardness or redness present, as well as the degree of pain reported for the time of the visit will be documented into the CRF.
- Solicited adverse events (local and general) that may have occurred since the vaccination will be documented in the CRF.
- Approximately 40-50 ml of blood will be collected for haematology, biochemistry, viral load, CD4 cell count and exploratory immunology.
- A photograph of the vaccination site will be taken. The subject will only be identifiable by a unique study number.

**Subsequent follow-up visits**

Volunteers will be reviewed at 28 (+/- 4 days), 84 (+/- 7 days) and 168 days (+/- 14 days) after the second vaccination.

- An interim history will be taken and, if considered necessary a physical examination emphasizing any acute complaints will be performed.
- Vital signs will be checked and documented
- The injection site will be inspected and the largest diameter of any hardness or redness present, as well as the degree of pain reported for the time of the visit will be documented into the CRF.
- Solicited adverse events (local and general) that may have occurred since the volunteer was seen on day 7 post second vaccination will be documented in the CRF.
- Approximately 32-42 ml of blood will be collected for exploratory immunology, viral load and CD4 cell count on days 28, 84 and 168 after the second vaccination. On day 84 after the second vaccination only, haematology and biochemistry will also be performed; therefore, the blood volume will be 40-50 ml.

## **6 STUDY INTERVENTION / INVESTIGATIONAL PRODUCT**

### **Study Product Acquisition**

#### **Formulation, Packaging and Labelling**

MVA85A is manufactured to Good Manufacturing Practice conditions by Impfstoffwerk Dessau-Tornau (IDT), Germany, for Oxford University. It is supplied in glass vials. These vials are clearly labelled with MVA85A.

#### **Product Storage and Stability**

MVA85A will be stored at  $-80^{\circ}\text{C}$  in a locked freezer at Laboratoire de Bactériologie-Virologie, CHU Le Dantec, Dakar.

#### **Preparation, Administration and Dosage of Study Intervention/Investigational Product**

The vaccine, MVA85A, is provided in vials of 200 microlitres volume at a concentration of  $7.4 \times 10^8$  pfu/ml in 10mM Tris buffer. The dose of MVA85A to be used in this study will be  $1 \times 10^8$  pfu (135 $\mu\text{l}$ ), this same dose will be given twice. On both vaccination days, the vaccine will be allowed to thaw to room temperature and administered within 1 hour. A single vaccine vial per subject to be immunised will be used on both vaccination days. The vaccine will be administered intradermally over the deltoid region of one arm. The investigator will wear gloves and eye protection. Subjects will stay in the unit for 60 minutes (+/- 10 mins) after vaccination for observation. During administration of the vaccines, medicines and resuscitation equipment will be immediately available for the management of anaphylaxis.

In order to minimise dissemination of the recombinant vectored vaccine virus into the environment the inoculation sites will be covered with a dressing after immunisation. This should absorb any virus that may leak out through the needle track. The dressings will be removed from the injection sites at the end of the 60 minute observation period and will be disposed as GMO waste by autoclaving, in accordance with the relevant SOP and current standard practice.

## **7 ASSESSMENT OF SCIENTIFIC OBJECTIVES (E.G., SAFETY OR IMMUNOGENICITY OR EFFICACY)**

### **Specification of the Appropriate Outcome Measures**

#### **Primary Outcome Measures:**

To assess the safety of two intradermal injections of  $1 \times 10^8$  pfu MVA85A, when administered to healthy subjects who are infected with HIV. The specific endpoints for safety and reactogenicity will be actively and passively collected data on adverse events (AEs).

#### **Secondary:**

To assess the effect of vaccination with MVA85A in healthy subjects who are infected with HIV on the immune response to antigen 85A (the antigen in the vaccine) and to ESAT-6 and CFP-10 (markers of TB infection).

The effect of a booster vaccination at six months will also be assessed.

A comparison between the immune responses by HIV-infected people who are not and are on ARVs will also be done.

The specific endpoints for immunogenicity will be markers of cell-mediated immunity as outlined below:

- Ex-vivo Elispot assay for interferon gamma: (exploratory immunology)

In all previous TB vaccine trials this has been the main immunological readout. However, there are as yet no validated cellular immunological assays and no perfect correlate of protection has been identified for TB. There is therefore ongoing work in the laboratory to develop other cellular assays including flow cytometry tests.

In view of this, other immunological assays may include:

- ex-vivo elispot assays for interleukin-2 and tumour necrosis factor alpha
- cultured elispot
- T cell proliferation
- whole blood assay for interferon-gamma
- T cell depletion assays
- cytokine detection using ELISA/LUMINEX or
- intracellular staining and FACScan analysis will be performed at the discretion of the investigators. (This also includes gene expression studies.)
- any other immunological assays that are developed during the timeline of the trial

## 8 ASSESSMENT OF SAFETY

All adverse events (AE) occurring in participants after administration of vaccine will be reported as described below.

### Definitions

#### Adverse Event

An AE is any untoward medical occurrence, including a dosing error, which may occur during or after vaccination.

The AE may or may not have a causal relationship with vaccination as indicated by physical signs, symptoms, and/or clinically significant laboratory abnormalities that occur. The definition includes intercurrent illnesses, injuries, exacerbation of pre-existing conditions, and events occurring as a result of product misuse or overdose.

A change in a laboratory variable is considered an AE if it leads to a change in the subject's functional status or if it is considered by the attending physician to be clinically significant. The following laboratory studies will be monitored during the course of this study (as previously outlined): full blood count (FBC), urea, creatinine, ALT, total bilirubin, albumin, alkaline phosphatase, sodium and potassium.

Adverse events will be graded and reported as detailed below.

Expected local reactions to the vaccine will not be recorded as an adverse event, but will be recorded on the CRFs. These include:

- Redness
- Swelling
- Pruritus
- Scaling
- Localised pain

